### Study participants (*N* = 510; 255 from each group)

The inclusion criteria for the study participants are: rural household with an adult male and female member (>18 years age), woman respondent who is able to provide consent for the study, the woman respondent is the primary cook of the house, senior most male respondent (or primary male decision maker in the household) who is able to provide consent for the study, women respondent residing in the household for the last 12 months, women respondent plans to reside in the household for at least 12 months from the date of enrollment for the study. An additional inclusion criterion for case group (LPG adopter households) is: household has received the first LPG cylinder in the last 12 months from the date of enrollment for the study.

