## Methods

### Study aim

This paper is part of our larger study aimed at exploring the determinants of adoption and sustained use of LPG in resource poor communities of rural India. The study is guided by the RE-AIM (Reach, Effectiveness, Adoption, Implementation, and Maintenance) implementation sciences framework. This protocol paper highlights the application of the RE-AIM framework in our study of LPG implementation in poor households. The overarching goal of our study is to derive new insights on the reach of LPG among the poor in rural India, factors that influence adoption (initial uptake), sustained use, and maintenance of LPG in below poverty line (BPL) households in rural India. Our specific aims are:To understand how below poverty LPG adopters vary from other BPL households on factors of affordability, accessibility, and awareness of LPG.To determine how affordability, accessibility, and awareness affect sustained and exclusive use of LPG in adopter households.To evaluate the relative influence of gender networks on LPG adoption and sustained use in BPL households.

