We use a multistage random sampling to select households in these rural habitations. To facilitate sample selection, we develop an exhaustive list of habitations (and households in these habitations) with four key variables: 1) distance to nearest LPG distribution center; 2) dominant caste of the habitation; 3) number of households in each habitation; 4) presence of LPG adopters in these habitations. A multistage sample selection process will be conducted using the following steps in their respective order:
**Sample of habitations:** We will use stratified random sampling to select the list of villages for the study. The selection criteria are:

*Proximity to the nearest LPG distribution center:* Based on the distance from the nearest LPG refilling and distribution center, we divide the exhaustive list of habitations (i.e. habitations population list) in two sub-groups: near to the center and far from the center, by taking a median split of the distance of the habitation from the LPG distribution center.
*Dominant caste of the habitation:* We divide the habitations population list into three sub-groups: General Caste, Other Backward Castes (OBC), and Scheduled Castes/Scheduled Tribes (SC/ST).

These two stratifying variables and their subgroups will lead to six distinct strata (2subgroups*3subgroups). We will divide the habitations population list across these six distinct strata. We will select a total sample of 35 habitations from these six distinct strata. Table 1 shows an indicative list of the six distinct strata that will be used to select the final 35 habitations.2.We have data on the number of LPG adopters and non-adopters from each of these selected habitations. We will use quota sampling to select households from each of these habitations. We will randomly select 255 LPG adopter households (case) from these 35 habitations. Subsequently, we will select as many non LPG adopter households (control) as we have LPG adopters (case) across each of the habitations. This will ensure a case control design in every habitation, with a control to case ratio as 1, and a total sample size of 510 households.

**Table 1 Tab1:** Exhibit list of stratified random sample of habitations

Strata	Proximity to LPG distribution centers	Dominant caste
1	Near	General
2	Near	OBC
3	Near	SC/ST
4	Far	General
5	Far	OBC
6	Far	SC/ST

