### Data collection

#### Aim 1: To understand how rural LPG adopters vary from other rural households on factors of affordability, accessibility, and awareness of LPG

A structured household adoption questionnaire will be used to record data on social, economic, and demographic characteristics. Women (primary cook) from each household will be the respondent for this questionnaire. In addition to household demographic characteristics, the questionnaire will record data pertaining to the 3 significant drivers impacting LPG adoption: affordability, accessibility, and awareness (3As) of LPG. The categorical outcome variable for aim 1 will be adoption of LPG at the time when data collection is undertaken for the household. Candidate variables on affordability include household income, upfront costs to acquire LPG, access to bank loans, facility of payment in installments for LPG purchase and refill, regularity of income (in past 12 months), and women’s financial autonomy. Candidate variables on accessibility include distance of habitations and households from LPG distribution centers, presence of paved roads to LPG distribution centers, and nature of LPG cylinders’ home delivery system. Candidate variables for awareness include government promotion campaigns, local self-government *(Gram Sabha)* awareness drives, and participation of women in self-help groups. In addition, we will capture data on how organizations at the community level, including government entities, and LPG distributors shape household adoption and sustained use of LPG. Candidate organizational factors are irregular supply and bureaucratic hurdles to apply for LPG, which will be assessed from the perspective of households. Key control variables that will be recorded are caste, household size, months of LPG ownership (in case group), educational status of household head, and free availability of biomass. This adoption questionnaire for aim 1 will be administered to all 510 households immediately after their enrollment in the study.

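### The target population is inconsistent: the Study aim section names below-poverty-line households, but sampling and eligibility neither restrict to nor identify them, and aims 1 and 3 later become aims about rural households

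*Protocol article*

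**What the plan says.** The Study aim section of the protocol article gives the overall goal as insight into reach, adoption, sustained use and "maintenance of LPG in below poverty line (BPL) households in rural India". Aim 1 there asks "how below poverty LPG adopters vary from other BPL households on factors of affordability, accessibility, and awareness of LPG". Aim 3 there reads "To evaluate the relative influence of gender networks on LPG adoption and sustained use in BPL households".

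Under Data collection, and again under Data analysis, aim 1 becomes "To understand how rural LPG adopters vary from other rural households on factors of affordability, accessibility, and awareness of LPG". Aim 3 is likewise reworded for rural households in both sections. Aim 2 refers to adopter households throughout and does not change population; poverty reaches it only through the overall goal.

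Sampling and recruitment states "we develop an exhaustive list of habitations (and households in these habitations", with four variables: distance to the distribution centre, dominant caste, number of households and presence of LPG adopters. Habitations are stratified on the first two. Then 255 adopters are drawn at random, with an equal number of non-adopters per habitation.

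The Study participants section begins "The inclusion criteria for the study participants are: rural household with an adult male and female member (>18 years age". It goes on to consent, the woman being the primary cook, a male decision maker, and past and planned residence. Cases must also have received a first LPG cylinder within the previous 12 months. No poverty, income or programme criterion appears for either group.

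**The concern.** The same aim numbers are attached to two different populations, and the operative rules match only the wider one. This matters more here than a mismatch on some incidental characteristic would, because poverty status is closely tied to the exposure under study. Household income is an affordability variable in aim 1, and the sample size was set on the income difference between adopters and non-adopters. If non-poor households are more common among cases than among controls, that difference partly measures poor against non-poor rather than what separates adopters from non-adopters among the poor. Drawing equal numbers of cases and controls within each habitation balances location but not household poverty.

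Even with no such imbalance, the results would describe a mixed rural population. The RE-AIM section defines reach partly by whether participants represent the target population, which cannot be judged while that population is stated in two ways. The Limitations section does not mention the issue.

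**Working it through.** **1. The sections side by side**

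- Study aim: goal, aim 1 and aim 3 are set in BPL households.
- Data collection and Data analysis: aims 1 and 3 are set in rural households.
- Sampling and recruitment: no poverty variable among the four listed and no poverty restriction in either draw.
- Study participants: no poverty criterion, general or case-specific.
- RE-AIM section: LPG dissemination in these communities is described as part of pro-poor government projects, but no section makes participation in one a condition of entry.

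Nothing in the stated rules therefore turns the sampled population into the one named in the Study aim section.

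**2. The protocol's own sample size**

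Inputs from Sampling and recruitment: mean monthly income difference 545.35 INR, common SD 2199.26 INR, two-sided alpha 0.05, ratio 1:1, 255 per group, power 80%.

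- Standardised difference: 545.35 / 2199.26 = 0.248.
- n per group = 2 × (1.960 + 0.842)² / 0.248² ≈ 255.3, or 256 rounded up (t-test version 256.3).
- Power at 255 per group = Φ(0.248 × √(255/2) − 1.960) = Φ(0.840) = 79.95% (t-test version 79.8%).

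The stated 255 and 80% are reproduced within rounding. The point does not rest on an error there.

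**3. Power if only the BPL households among the 510 address the stated aims**

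The documents give no BPL share. The shares below are assumptions, taken as equal in both groups, with the income difference and SD unchanged.

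| Assumed BPL share | n per group | Power |
|---|---|---|
| 90% | 229 | 76% |
| 80% | 204 | 71% |
| 70% | 178 | 65% |
| 50% | 127 | 51% |
| 30% | 76 | 33% |

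For example, at 80%: Φ(0.248 × √(204/2) − 1.960) = Φ(0.544) = 71%. With unequal shares, such as 50% of cases and 80% of controls, power is about 59%.

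**4. What a mixture could do to the raw income difference**

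Shift = (non-poor share in cases − non-poor share in controls) × income gap between non-poor and poor. Neither the shares nor the gap is in the document. Assuming, for illustration only, a gap of one stated SD (2199 INR):

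- equal shares: 0 INR;
- 10% against 0%: 0.10 × 2199 = 220 INR;
- 30% against 15%: 0.15 × 2199 = 330 INR;
- 30% against 0%: 0.30 × 2199 = 660 INR;
- 10% against 30%: −0.20 × 2199 = −440 INR.

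The planned difference is 545 INR. The shift could be nil, material or negative, and the document does not allow a choice between these.

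**The case against.** A reader might infer that the study cannot answer its own question. The documents do not support that. Household income and its regularity are to be recorded for all 510 households, so a poverty-restricted or income-stratified analysis may be possible with fewer households. The setting is described as poor communities, so many sampled households may be BPL. Against the rural wording of aims 1 and 3, the sample fits.

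A reader might also infer that non-poor households will be over-represented among cases and that the affordability effect is therefore inflated by a known amount. The section on LPG supply does say that poor households account for only a small part of LPG use, but this concerns total fuel consumption, not who newly adopts in two rural mandals. Cases must have had a first cylinder within 12 months, which excludes long-standing users. No rule keeps non-poor households out of the controls, so a zero share there is an extreme assumption. Aim 1 is also analysed by regression of adoption on the predictors. A wider income range raises the raw mean difference but does not by itself bias the income coefficient if the relation is linear on the logit scale.

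Finally, the article condenses a fuller protocol, its variable lists are given as candidates, and the study calls itself primarily exploratory. A BPL item missing from those lists is not a finding.

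These arguments remove any claim of demonstrated inflation. They do not remove the conflict between the Study aim section and the later sections, or the absence of a poverty rule in the stated selection criteria.

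**Conclusion.** The point holds as an inconsistency in the target population. Following the plan exactly would produce a sample not restricted to the population named in the goal and in aims 1 and 3 of the Study aim section. This changes who the conclusions apply to, and it leaves open that the income and affordability contrast partly reflects poor versus non-poor. It is therefore more than a missing detail.

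No bias figure can be given: size and direction depend on the unknown difference in non-poor share between cases and controls, and equal shares give none. What can be stated, assuming equal BPL shares and the protocol's own income difference and SD, is the price of falling back on a BPL subset: power drops from about 80% to about 71% if 80% of households are BPL, and to about 51% if half are.

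**What to change.** Before sampling, choose one of three repairs and use it consistently in all sections.

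1. Make BPL status an eligibility criterion, applied equally to cases and controls. If too few BPL adopters are found, use the existing rule in Sampling and recruitment for adding habitations. Recheck the income difference and SD behind the sample size, since both could differ in a BPL-only sample. If they do not, 255 per group still gives about 80% power.
2. Keep eligibility as it is, record BPL status for all 510 households, and pre-specify the BPL households as the analysis set for the aims as worded in the Study aim section. State the reduced power, and report results for non-BPL households separately.
3. Restate the goal, aims 1 and 3 and the conclusions for rural households. This is the simplest repair, but it gives up the question posed in the Study aim section.

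The cost is modest before enrolment. Option 1 needs BPL status on the household list, which is not among its four stated variables, and may need more habitations. Option 2 needs BPL status from the questionnaire and accepts lower power. Option 3 needs only rewording.

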### Data collection

#### Aim 1: To understand how rural LPG adopters vary from other rural households on factors of affordability, accessibility, and awareness of LPG

A structured household adoption questionnaire will be used to record data on social, economic, and demographic characteristics. Women (primary cook) from each household will be the respondent for this questionnaire. In addition to household demographic characteristics, the questionnaire will record data pertaining to the 3 significant drivers impacting LPG adoption: affordability, accessibility, and awareness (3As) of LPG. The categorical outcome variable for aim 1 will be adoption of LPG at the time when data collection is undertaken for the household. Candidate variables on affordability include household income, upfront costs to acquire LPG, access to bank loans, facility of payment in installments for LPG purchase and refill, regularity of income (in past 12 months), and women’s financial autonomy. Candidate variables on accessibility include distance of habitations and households from LPG distribution centers, presence of paved roads to LPG distribution centers, and nature of LPG cylinders’ home delivery system. Candidate variables for awareness include government promotion campaigns, local self-government *(Gram Sabha)* awareness drives, and participation of women in self-help groups. In addition, we will capture data on how organizations at the community level, including government entities, and LPG distributors shape household adoption and sustained use of LPG. Candidate organizational factors are irregular supply and bureaucratic hurdles to apply for LPG, which will be assessed from the perspective of households. Key control variables that will be recorded are caste, household size, months of LPG ownership (in case group), educational status of household head, and free availability of biomass. This adoption questionnaire for aim 1 will be administered to all 510 households immediately after their enrollment in the study.

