### Sampling and recruitment

We will undertake a case control study in the rural habitations of Thambalpalle and Peddamandyam mandals (block) in Chittoor district of Andhra Pradesh state in India [27]. Our implementing partner, Foundation for Ecological Security (FES) has extensive field experience working in this region and we will leverage their expertise and understanding of social, economic, and demographic characteristics of the households in these habitations.

We will select an equal number of case and control households for this proposed study (control to case ratio will be 1:1). We will select a sample size of 255 households each for case (LPG adopter households) and control (LPG non-adopter households). A total sample size of 510 households at a 95% confidence level (alpha = .05) will provide a power of 80% to this study at a control to case ratio of 1. This computation assumed that the populations mean difference in monthly income was 545.35 India National Rupee (INR), and the common within-group standard deviation was 2199.26 INR per month. In the absence of previously published studies on rural income in this region, where the study is to be undertaken, the power computation was conducted using a baseline income data from another recently concluded NIH funded R21 (WUSTL IRB ID# 201207016) randomized controlled trial (RCT) on cookstoves. This study will be conducted in the same region where the RCT was undertaken. To calculate the sample size, we used the Power and Precision 4 software. The criterion for significance (alpha) was set at 0.05. The test was 2-tailed, and so an effect in either direction will be interpreted. With the proposed sample size of 255 each for case and control group, the study will have power of 80% to yield a statistically significant result. It is also assumed that this effect size is reasonable; an effect of this magnitude could be anticipated in this field of research. On average, a study of this design would enable us to report the mean income difference with a precision of 95% confidence level.

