### Limitations

There are limitations of this study. Each of these limitations is briefly considered below.
**Study design:** The retrospective nature of aim 1 and aim 3 in the study for LPG adopters might lead to concerns of recall bias, which may limit the accuracy of participants’ memories on factors of 3As, which impacts adoption. However, engaging a large sample size of 510 households in such geographically proximal households might reduce the issues of recall bias [43]. Similarly, the retrospective nature of data from follow-up questionnaire for aim 2 might also be subject to recall bias.
**Data analyses:** Regression of sustained use (SUMS data) on its determinants (3As) (from follow up questionnaires) will be done for a small sample size of 100 households. Smaller sample size might preclude us from conducting multilevel analyses by controlling for institutional level predictors.
**Exploratory study:** There is limited empirical evidence available on the impact of 3As on adoption and sustained use of LPG. This study is primarily exploratory and developmental in nature. However, it is expected that this study will inform future research to develop and test the effectiveness of implementation strategies for LPG adoption and use in resource poor settings within the RE-AIM framework. In addition, findings from the study will provide insights on the estimate of effect size to facilitate a larger R01 study on the impact of 3As on LPG adoption and sustained use in such communities.

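### Aim 1 regresses LPG adoption on answers collected up to 12 months after adoption, with no stated pre-adoption reference date, and lists as a control a variable defined only for adopters

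*Protocol article*

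**What the plan says.** - **Who is a case.** The extra inclusion criterion in Study participants is: "household has received the first LPG cylinder in the last 12 months from the date of enrollment for the study".
- **When aim 1 is measured.** Data collection, Aim 1, gives the questionnaire to all 510 households straight after enrolment and takes adoption status at that same time as the outcome.
- **What is measured.** The same section presents affordability, accessibility and awareness (the 3As) as drivers of adoption. Only one candidate variable has a stated look-back: "regularity of income (in past 12 months", counted from the interview. Irregular supply and bureaucratic hurdles are assessed as households perceive them.
- **Control variables.** "Key control variables that will be recorded are caste, household size, months of LPG ownership (in case group"; the list continues with education of the household head and free availability of biomass.
- **Model.** Data analysis, Aim 1, regresses adoption (yes/no) on the 3As from this questionnaire, with a multilevel model by habitation if the intraclass correlation exceeds 5%. It does not list the control variables that enter.
- **Acknowledged limits.** Limitations admits possible recall bias for adopters and then says that "engaging a large sample size of 510 households in such geographically proximal households might reduce the issues of recall bias". It does not mention reverse causation.

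**The concern.** A case-control analysis of determinants needs exposures that refer to a time before the outcome, with a comparable time in controls. Here the outcome has already occurred in every case when the questions are asked, and nothing in the article moves the reference point back. A household's income pattern, a woman's say over money, her membership of a self-help group, or her view of supply problems may differ because the household now owns LPG. The regression cannot tell this from a difference that led to adoption.

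Months of LPG ownership is a separate fault. It has no value in a control, so it cannot adjust a comparison of adopters with non-adopters.

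The recall-bias sentence matters because it presents a systematic error as if more households would lessen it. Limitations also intends the effect sizes to inform a larger study, so any bias would carry forward. The regression can be respecified after data collection; answers without a reference date cannot be repaired.

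**Working it through.** **1. The plan's own figure.** Inputs from Sampling and recruitment: two-sided alpha 0.05; 80% power with 255 households per group; "the populations mean difference in monthly income was 545.35 India National Rupee (INR"; SD 2,199.26 INR in both groups; ratio 1:1.

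- Standardised difference: 545.35 / 2,199.26 = 0.248.
- n per group = 2 × (1.960 + 0.842)² / 0.248² ≈ 255.3, rounded up to 256.
- Power at 255 per group: 79.95% (normal approximation), 79.8% (t-test).

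The stated 255 and 80% are reproduced. The sample size is not at issue.

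**2. Timing.** Let t be the months from first cylinder to enrolment. The inclusion criterion gives 0 ≤ t ≤ 12, and the interview follows enrolment, so each case answers about t months after adoption. For an item with a 12-month look-back, the share of the window after adoption is t/12, with range 0 to 100%. If t were uniform on 0 to 12 (an assumption), the mean share would be 6/12 = 50%. This applies to income regularity alone, the only item with a stated window. It measures overlap of time, not bias in an estimate.

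**3. Which items are exposed.**

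| Ownership could change or reveal it | Largely unaffected |
|---|---|
| Income and its regularity | Caste |
| Women's financial autonomy | Distance to the distribution centre |
| Self-help group participation | Paved roads |
| Perceived supply and bureaucratic hurdles | Campaigns and delivery facility (classed as community level in Data analysis) |

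**4. Months of ownership in the aim 1 model.**

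- *Coded 0 in controls:* the value is above 0 in every case and 0 in every control. The logistic likelihood rises without limit as the coefficient grows, so no finite estimate exists. In a simulated check (255 cases with 0.1 to 12 months, 255 controls with 0) the area under the ROC curve was 1.0 and the fit failed with a singular matrix.
- *Coded missing in controls:* 510 − 255 = 255 households remain, all cases, and the outcome no longer varies.

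**5. What a post-adoption shift could do.** The documents give no shift size, so these are assumptions. Suppose no difference before adoption and a shift of δ SD after it, tested with a two-sided t-test at 255 per group, ignoring clustering. The non-centrality is δ × √(255/2) = 11.29δ.

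| δ (SD) | On the income scale (δ × 2,199.26 INR) | Declared significant |
|---|---|---|
| 0 | 0 | 5% |
| 0.05 | 110 | 9% |
| 0.10 | 220 | 20% |
| 0.15 | 330 | 39% |
| 0.20 | 440 | 62% |

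**6. Sample size and systematic error.** The standard error of a difference is SD × √(2/n) and shrinks with n; a systematic shift does not. For δ = 0.10, doubling to 510 per group gives non-centrality 0.10 × √(510/2) = 1.60, and P(Z > 1.96 − 1.60) ≈ 0.36. The false-positive rate would rise from 20% to about 36%.

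**The case against.** The case on the other side has weight.

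- *The model that cannot be fitted is not in the article.* The controls are variables to be recorded, Data analysis never says that ownership months enters the adoption model, and the restriction to the case group shows the authors know it is case-only. A reader might infer that the aim 1 model as planned must fail; the text does not support that. What stands is that the variable is listed as an aim 1 control with no stated limit on its use.
- *Many predictors cannot follow from one household's ownership.* Controls come from the same habitations as cases in equal numbers, and roads, distance, campaigns and delivery facility are community characteristics. This stands, and it confines the concern to time-varying household items.
- *The questionnaire is not shown.* Limitations calls aim 1 retrospective for adopters and refers to their memories of the 3As, so some items may ask about conditions at the adoption decision. This stands as a reason to say that effects may be misread, not that they will be. It does not supply a reference date, and the one window given runs back from interview.
- *The aim is to describe how adopters differ, and the study is declared exploratory.* This lowers the stakes. However, the article also calls the 3As drivers and predictors of adoption, which is a directional reading.
- *The text says only that sample size might reduce recall bias.* The hedge does not rescue the reasoning: neither the number of households nor their proximity removes a systematic error.

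**Conclusion.** The point holds in limited form. Aim 1 does not secure temporal order for time-varying household items, because cases answer 0 to 12 months after adoption with no stated earlier reference date. One listed control is defined only for cases and cannot serve in the adopter versus non-adopter model. The sentence offering sample size against recall bias is wrong.

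The bias itself cannot be sized from the article. The 50% overlap concerns one item and rests on evenly spread adoption dates. The 9% to 62% false-positive rates rest on assumed shifts of 0.05 to 0.20 SD. A reader might also infer that awareness and supply effects will be inflated; the documents do not establish a direction. Sample size and stated power are unaffected. The matter should be settled before fielding, since the wording of the questions fixes what can be learned.

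**What to change.** 1. State that months of LPG ownership is used only in case-only analyses (aim 2) and not in the aim 1 model.
2. Record the first-cylinder date of each case as its index date. Give controls index dates drawn from the case dates in the same habitation. No control is paired with a case, but numbers are equal within habitations, so the case dates can be allotted at random, one to each control.
3. Word time-varying household items as status at, or shortly before, the index date. The window must fit the 12-month residence criterion: a woman whose index date lies t months back is guaranteed only 12 − t months of residence before it, which is 0 when t = 12. A full 12-month window before the index date could reach back 24 months and is not suitable.
4. In Limitations, delete the claim that sample size and proximity might reduce recall bias, and name reverse causation for time-varying household items.

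The cost is one date field, rewording of some items, a simple procedure for assigning index dates to controls, and somewhat longer recall in both groups. The number of households does not change.
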